### Sample size

Currently, an R0 resection is achieved in approximately 60 per cent of patients undergoing surgery after treatment with neoadjuvant chemoradiotherapy^16^^,^^17^. However, 25 per cent of patients who start neoadjuvant chemotherapy are not eligible for surgery owing to progressive disease: local progression, distant progression, or death from progression^12^. This means that an R0 resection is obtained in only 45 per cent of patients (75 per cent of 60 per cent) who start with intentionally curative treatment. The study hypothesis is that there will be a 15 per cent increase in the R0 resection rate (from 45 to 60 per cent) for patients in the experimental arm. A χ^2^ test with a 5 per cent two-sided significance level indicated that the study would have 80 per cent power to detect a significant difference of 15 per cent between the two groups (given that the percentage in the control group is 45 per cent) when the sample size in each group is 173 patients. With an expected dropout of 5 per cent, the total requirement was calculated as 364 patients.

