## Methods

### Study design and setting

This is a multicentre, international, open-label, phase III, parallel-arms study that will randomize eligible patients in a 1 : 1 ratio to receive either induction chemotherapy followed by neoadjuvant chemoradiotherapy and surgery (experimental arm) or neoadjuvant chemoradiotherapy and surgery alone (control arm). The study is registered with ClinicalTrials.gov (NCT04389086), including the list of centres enrolling for the trial. Surgical treatments will be limited to centres that perform at least 10 resections of LRRC per year (expert centres). Induction chemotherapy and chemoradiotherapy will be administered in expert centres and selected non-expert centres. This is protocol version 4.0, dated 10 December 2020.

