### Statistical methods

Demographics, patient, and tumour characteristics will be presented for each treatment arm. Continuous data will be reported as mean (standard deviation) or median (interquartile range or 95 per cent confidence interval), depending on the distribution. Categorical data will be reported as count with percentage. All statistical tests will be two-sided and *P* < 0.050 will be classified as statistically significant. Patients initially randomized but considered ineligible afterwards, based on information that should have been available before randomization, will be excluded from all analyses.

Analysis of the primary endpoint of this study, the proportion of patients with an R0 resection, will be based on the intention-to-treat principle using Fisher’s exact test. In addition, a per-protocol analysis will be performed as a sensitivity analysis.

All survival curves will be constructed according to the Kaplan–Meier method, and the log rank test will be used to compare treatment arms, adjusting for stratification factors at randomisation (previous radiotherapy, previous systemic therapy, and expert centre). In addition, hazard ratios will be calculated using a Cox proportional hazards regression model, adjusting for stratification factors. Metastasis-free survival, progression-free survival, and overall survival will be based on the intention-to-treat group. Local re-recurrence free survival and disease-free survival analyses will include only patients who underwent surgery.

Data on surgical characteristics, histopathological characteristics, and major surgical morbidity will be presented by treatment arm, and will be derived only for patients who underwent surgery. The number of patients undergoing surgery will be analysed in the intention-to-treat population. Comparison between treatment arms will be done by means of Fisher’s exact test.

The absolute and relative incidence of toxicities related to the administration of induction chemotherapy or chemoradiotherapy will be presented by treatment arm, and analysed in all patients who received at least one dose of neoadjuvant chemotherapy (experimental arm) or chemoradiotherapy (control arm). Comparison between treatment arms will be done by means of Fisher’s exact test.

Comparison of health-related quality of life between the two treatment arms at baseline and over time will be performed by means of a random-effects regression model and will be based on the intention-to-treat group.

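### The stated 80% power belongs to a χ² test, but the primary analysis is Fisher's exact test, which has 76.0% power at the stated 173 evaluable per arm and 79.6% if all 364 are analysed

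*Protocol article*

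**What the plan says.** The Sample size section of the protocol article gives its planning hypothesis: "there will be a 15 per cent increase in the R0 resection rate (from 45 to 60 per cent) for patients in the experimental arm". It states that a χ² "test with a 5 per cent two-sided significance level indicated that the study would have 80 per cent power" for this difference "when the sample size in each group is 173 patients". It then adds: "With an expected dropout of 5 per cent, the total requirement was calculated as 364 patients". Study design and setting gives equal allocation, so 364 means 182 per arm.

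The Statistical methods section names the test for the same endpoint: its analysis "will be based on the intention-to-treat principle using Fisher’s exact test". Significance is declared at a two-sided P below 0.050. The same section removes from all analyses any patient found ineligible on information that should have been available before randomization. Nothing in the article links the test used for sizing to the test used for analysis.

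**The concern.** A power figure describes one test at one sample size. Here the 80% describes a test that the trial does not plan to use for its primary comparison. Fisher's exact test conditions on the total number of R0 resections. At this sample size its rejection region is smaller than that of the uncorrected χ² test, so it has less power and does not spend the full 5% type I error.

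Two things are at stake. The chance of missing a true gain of 15 percentage points is higher than the 20% the protocol implies. There are also results on which the two tests disagree, so the choice can decide whether the trial is called positive. This is not a detail that an unseen analysis plan could be expected to supply, because the article names both tests explicitly.

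**Working it through.** **Inputs.** From Sample size: control rate 0.45, experimental rate 0.60, two-sided α = 0.05, 80% power, 173 per arm, 5% dropout, 364 in total. From Study design and setting: 1:1 allocation. From Statistical methods: Fisher's exact test, P < 0.050.

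**Step 1: reproduce the protocol's figure.** Pooled-variance formula without continuity correction:

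n = [z₀.₉₇₅ √(2p̄(1 − p̄)) + z₀.₈₀ √(p₁(1 − p₁) + p₂(1 − p₂))]² / (p₂ − p₁)², with p̄ = 0.525.

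- First term: 1.960 × √0.49875 = 1.3842.
- Second term: 0.8416 × √0.4875 = 0.5876.
- n = (1.9718)² / 0.0225 = 172.8, so 173 per arm.
- Total: 346 / 0.95 = 364.2, given as 364.

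The formula power at 173 per arm is 80.05%. The protocol's figure therefore reproduces, and only for the uncorrected χ² test. The continuity-corrected formula, which approximates Fisher's test, is (n/4)[1 + √(1 + 4/(n × 0.15))]² with n = 172.8. It gives 185.9, so 186 per arm.

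**Step 2: exact power and size.** List every pair (x₁, x₂) of R0 counts, mark those that each test rejects at P < 0.05, and sum Bin(x₁; n, 0.45) × Bin(x₂; n, 0.60) over the marked pairs. For the size, use the same rate in both arms. Doubling the one-sided P value instead of using the usual two-sided Fisher definition gives the same results at these sample sizes.

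| Analysed per arm | Power, χ² | Power, Fisher | Size at 45%, χ² | Size at 45%, Fisher |
|---|---|---|---|---|
| 173 | 79.2% | 76.0% | 4.7% | 3.6% |
| 178 | 81.1% | 78.1% | 4.9% | 3.8% |
| 180 | 81.8% | 78.9% | 5.0% | 3.9% |
| 182 (all randomized) | 82.5% | 79.6% | 5.1% | 4.0% |
| 183 | 82.8% | 80.0% | 5.2% | 4.0% |

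Over common rates from 30% to 70%, the χ² size peaks at about 5.2% at both 173 and 182 per arm. Fisher's size lies between 3.6% and 4.1%.

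**Step 3: size needed for Fisher's test.** It first reaches 80% at 183 evaluable per arm (80.02%). That is 366 evaluable, and 366 / 0.95 = 385.3, so 386 in two equal arms against the 364 planned.

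**Step 4: a result on which the tests disagree.** With 78/173 (45.1%) against 97/173 (56.1%), the uncorrected χ² test gives P = 0.041 and Fisher's test gives P = 0.053.

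**The case against.** The best counter-argument is that 76% is the bottom of a range. The trial randomizes 364 and analyses by intention to treat. If all 182 per arm contribute at the full planning rates, Fisher's test has 79.6% power, which is close to the stated 80%. This stands in part, and it is why 76% should not be quoted without its sample size. It does not remove the point. The 5% was added because losses are expected, some patients may be excluded as ineligible, and even the best case stays just under 80%.

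Second, like for like, the choice of test costs about 3 points: 79.2 to 76.0 at 173 per arm, and 82.5 to 79.6 at 182. The rest of the gap to 80% comes from the normal approximation. Planning uncertainty is at least as large: a 16-point effect would give Fisher's test 81.5% at 173 per arm. This stands, and it limits the weight of the point.

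Third, Fisher's test is valid and guarantees the level, which the χ² test does not do exactly. This also stands.

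A reader might go further and infer any of the following, none of which the document supports:

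- **The sample size arithmetic is wrong.** It reproduces for the test it names.
- **The trial's conclusion would be unsafe.** The departure is conservative and does not bias the estimate.
- **Power is really about 75%.** Counting the 5% dropouts as not R0 among 182 per arm (42.75% against 57.0%) gives 75.3% for Fisher's test. The article states no such rule, and the χ² test itself falls to 78.5% under it.
- **The χ² test costs nothing.** A size of 4.7% holds at 173 per arm and a 45% rate. It is 5.1% at 182 per arm.

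**Conclusion.** The point holds as a moderate inconsistency. The specified primary test does not deliver the stated power at the stated evaluable sample size: 76.0% instead of 80% at 173 per arm. The chance of missing the design effect is then 24.0% instead of 20%. With complete analysis of all 364 patients, power is 79.6%.

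These figures assume true rates of exactly 45% and 60%, equal arms, independent patients and an unstratified comparison. Type I error is controlled and the estimated difference in R0 rates is the same under either test. What needs correcting is the mismatch between the two sections, not the trial's validity.

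**What to change.** **Preferred: make the test match the sizing.** Name the uncorrected χ² test as the primary test, or its Mantel-Haenszel form stratified by the randomization factors, and keep Fisher's exact test as a sensitivity analysis. No extra patients are needed. Because the trial is open-label, the change should be made by documented amendment before anyone has seen comparative outcome data. A later move to the less conservative test would be hard to defend. The small cost is that the exact size of the χ² test can reach about 5.2%. The power of the stratified form was not computed here.

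**Alternative: keep Fisher's test and correct the figure.** The Sample size section would state about 76% power at 173 evaluable per arm, rising to 79.6% if all 364 are analysed. This changes one sentence and leaves the analysis as it is. Holding 80% with Fisher's test would instead need 183 evaluable per arm, or 386 randomized with the same 5% allowance: 22 more than planned, in a disease that the Discussion describes as relatively rare.

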### Statistical methods

Demographics, patient, and tumour characteristics will be presented for each treatment arm. Continuous data will be reported as mean (standard deviation) or median (interquartile range or 95 per cent confidence interval), depending on the distribution. Categorical data will be reported as count with percentage. All statistical tests will be two-sided and *P* < 0.050 will be classified as statistically significant. Patients initially randomized but considered ineligible afterwards, based on information that should have been available before randomization, will be excluded from all analyses.

Analysis of the primary endpoint of this study, the proportion of patients with an R0 resection, will be based on the intention-to-treat principle using Fisher’s exact test. In addition, a per-protocol analysis will be performed as a sensitivity analysis.

All survival curves will be constructed according to the Kaplan–Meier method, and the log rank test will be used to compare treatment arms, adjusting for stratification factors at randomisation (previous radiotherapy, previous systemic therapy, and expert centre). In addition, hazard ratios will be calculated using a Cox proportional hazards regression model, adjusting for stratification factors. Metastasis-free survival, progression-free survival, and overall survival will be based on the intention-to-treat group. Local re-recurrence free survival and disease-free survival analyses will include only patients who underwent surgery.

Data on surgical characteristics, histopathological characteristics, and major surgical morbidity will be presented by treatment arm, and will be derived only for patients who underwent surgery. The number of patients undergoing surgery will be analysed in the intention-to-treat population. Comparison between treatment arms will be done by means of Fisher’s exact test.

The absolute and relative incidence of toxicities related to the administration of induction chemotherapy or chemoradiotherapy will be presented by treatment arm, and analysed in all patients who received at least one dose of neoadjuvant chemotherapy (experimental arm) or chemoradiotherapy (control arm). Comparison between treatment arms will be done by means of Fisher’s exact test.

Comparison of health-related quality of life between the two treatment arms at baseline and over time will be performed by means of a random-effects regression model and will be based on the intention-to-treat group.

Incremental cost-effectiveness and cost–utility ratios will be calculated for the extra costs per additional surviving patient and the extra costs per additional quality-adjusted life year respectively. Non-parametric bootstrapping, drawing samples of the same size as the original samples and with replacement, will be applied to generate 95 per cent confidence intervals for (differences in) costs and health outcomes. Cost-effectiveness planes will be displayed and cost-effectiveness acceptability curves drawn for willingness-to-pay values up to €100 000.

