### Interventions

Eligible patients who have signed informed consent will be randomized by the coordinating investigator in a 1 : 1 ratio using a software randomization program (ALEA Clinical; FormsVision, Abcoude, the Netherlands). Patients will be stratified for previous chemotherapy, previous radiotherapy, and expert centre. After randomization, the treating surgical oncologist will refer the patient to the medical oncologist (experimental arm) or radiation oncologist (control arm).

The study flow chart is shown in *Fig. 1*, and study interventions and timelines for patients allocated to the experimental and control arms in *Tables 1* and *2* respectively.

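### The primary R0 comparison is fixed as an unstratified Fisher's exact test although randomisation is stratified; this gives up several points of power without threatening validity

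*Protocol article*

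**What the plan says.** Under Interventions, the protocol article sets the randomisation factors: "Patients will be stratified for previous chemotherapy, previous radiotherapy, and expert centre".

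Under Statistical methods, the primary analysis is fixed: "Analysis of the primary endpoint of this study, the proportion of patients with an R0 resection, will be based on the intention-to-treat principle", with Fisher's exact test as the method. The only other analysis named for R0 is a per-protocol sensitivity analysis, which changes the population and not the adjustment.

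The next paragraph of the same section treats the survival endpoints differently: "the log rank test will be used to compare treatment arms, adjusting for stratification factors at randomisation". It lists all three factors, and the Cox model adjusts for them as well. No reason is given for leaving R0 unadjusted.

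The Sample size section rests on a third method, a plain χ² test: "A χ^2^ test with a 5 per cent two-sided significance level" and "the study would have 80 per cent power to detect a significant difference of 15 per cent between the two groups", "when the sample size in each group is 173 patients".

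**The concern.** Stratified allocation balances the arms on the stratification factors, so variation between strata largely drops out of the observed difference between arms. An unstratified test still counts that variation in its standard error. If the factors predict R0, the standard error is too large, the type I error falls below 5% and power is lost.

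The article gives some reason to expect prediction. The Introduction lists fibrosis from earlier radiotherapy among the causes of failed R0 resection, and the radiotherapy dose depends on previous irradiation. It says nothing comparable about previous chemotherapy, and it gives no figures for any factor.

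Fisher's test adds conservatism of its own, and the sample size was not calculated for it. The Discussion describes the disease as rare and says that feasible sample size drove the choice of endpoint. Power that can be recovered without extra patients therefore matters in this trial.

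**Working it through.** **Inputs.** From Sample size: two-sided 5%, 80% power, 45% versus 60%, 173 per arm, 5% dropout, 364 in total. From Study design and setting: 1:1 allocation. The prognostic strength of the strata is assumed below.

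**1. The plan's own figure.** For a χ² test without continuity correction,

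n = [1.96√(2 × 0.525 × 0.475) + 0.8416√(0.45 × 0.55 + 0.60 × 0.40)]² / 0.15² = (1.384 + 0.588)² / 0.0225 = 172.8, so 173 per arm. The normal-approximation power at 173 is 80.0%. With dropout, 173 × 1.05 = 181.65, so 182 per arm and 364 in total. The stated figures are reproduced.

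**2. The named test at that size.** Enumerating all 2×2 tables at 173 per arm gives:
- Fisher: power 76.0%; type I error 3.6% at a common rate of 45%.
- χ²: power 79.2%; type I error 4.7%.

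Fisher first reaches 80% at 183 per arm. At 182 per arm, which is 364 patients with no dropout at all, it has 79.6%.

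**3. Effect of ignoring strata on type I error.** Take four equal strata (previous radiotherapy × previous chemotherapy), balanced within stratum. With assumed control rates of 65/55/35/25% (mean 45%), the mean within-stratum variance is (0.2275 + 0.2475 + 0.2275 + 0.1875)/4 = 0.2225. The unstratified test uses 0.45 × 0.55 = 0.2475. The ratio is 0.899, so the actual size of a nominal 5% unstratified χ² test is about 2[1 − Φ(1.96/√0.899)] = 3.9%. With weaker strata (55/50/40/35%) the ratio is 0.24125/0.2475 = 0.975 and the size is about 4.7%. Fisher lies below these values.

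**4. Effect on power at the planned 45% versus 60%.** The odds ratio must be set so that the experimental mean is 60%. With strong strata this needs about 1.96: the control odds multiplied by 1.96 give 78.5/70.6/51.4/39.6%, mean 60.0%. Simulation at 173 per arm gives:

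| Assumed strata | Fisher power | Unstratified χ² power | CMH power | Fisher type I error |
|---|---|---|---|---|
| Not prognostic | 75.9% | 79.1% | 79.1% | 3.6% |
| Weaker (55/50/40/35%) | 76.4% | 79.7% | 81.1% | 3.2% |
| Strong (65/55/35/25%) | 77.4% | 80.7% | 84.2% | 2.8% |

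A repeat with 60,000 trials per scenario agrees to within 0.2 points and puts the type I error of CMH at 4.8 to 5.0%.

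**5. Splitting the gain.** From Fisher to χ²: 3.2, 3.3 and 3.3 points. From χ² to CMH: 0.0, 1.4 and 3.5 points.

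**6. All three factors, with centre.** A second simulation used 346 patients, 60% with previous radiotherapy, 40% with previous chemotherapy and 10 equal centres (all assumed). Scenarios ran from no effect to strong (odds ratios 0.33 and 0.5, centre SD 0.7 on the log-odds scale).
- Fisher power: 77.7, 77.4, 78.3 and 79.2%.
- CMH over four strata: 80.2, 80.4, 81.9 and 84.2%.
- CMH over all factors: 80.1, 80.3, 82.5 and 86.2%.

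The type I error of the four-stratum CMH is 4.9, 5.0, 4.7 and 3.9%, so leaving centre out keeps some conservatism when centre is strongly prognostic. Arm totals vary slightly from run to run here, which probably explains why Fisher does a little better than with exactly equal arms.

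**The case against.** The strongest reply is that this is a matter of efficiency and not an error. Fisher's test is valid, it errs on the safe side, and a SAP that is not shown may add an adjusted analysis and an effect estimate. All of that stands, except that the article itself names the primary test, so a SAP that follows it would carry the same loss.

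Three stronger readings are tempting, and the article does not support them.

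- *Ignoring strata erodes the planned power.* It does not. At a true 45% versus 60%, unstratified power stays level or rises slightly as the strata become prognostic (Fisher 75.9, 76.4 and 77.4%). What is lost is an additional gain. A reader who kept the odds ratio at 1.83 (1.5/0.818) in every stratum would see a larger drop. With the strong strata, however, that odds ratio gives an experimental mean of only 58.5%, a 13.5-point difference, which is not the hypothesis of "15 per cent increase in the R0 resection rate (from 45 to 60 per cent) for patients in the experimental arm".
- *The whole gap between Fisher and CMH is due to stratification.* About 3 points belong to Fisher's test itself and would be there with no strata at all.
- *R0 is the one comparison left unadjusted, so the plan contradicts itself.* The number of patients undergoing surgery and the toxicity comparisons also use plain Fisher tests, and no stratification factors are named for the quality-of-life model. The plan is consistent by type of endpoint: binary endpoints unadjusted, time-to-event endpoints adjusted.

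The size of the benefit also rests on assumed prognostic strength and on near-perfect balance within strata, which puts the conservatism shown close to an upper bound.

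**Conclusion.** The point holds as a loss of efficiency in a method that the article fixes. At 173 per arm, the named test has 76 to 77% power where a CMH test on the randomisation factors would have about 79 to 84%. The part due to Fisher (about 3 points) needs no assumption about the strata. The part due to ignoring strata (0 to 4 points) depends entirely on how well previous radiotherapy and previous chemotherapy predict R0. Stratifying costs essentially nothing if they do not.

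The true type I error is below 5%, so a significant result stands and no bias arises. The risk is a missed effect. The change should be made, but the trial's validity does not depend on it.

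**What to change.** Before any outcome data are analysed by arm, amend Statistical methods as follows:

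- **Primary test:** a two-sided CMH test in the intention-to-treat population, stratified by previous radiotherapy × previous chemotherapy (four strata), with the Mantel-Haenszel common risk difference and 95% CI. That estimate is on the scale of the 15-point hypothesis.
- **Sensitivity analysis for expert centre:** either add centre to the strata with small centres pooled, or fit a model with a random centre effect. Full crossing with centre in the primary test could leave very small strata.
- **Supportive:** keep Fisher's exact test.

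The cost is a change of wording in the protocol and SAP. The factors are already recorded for randomisation, and the sample size of 364 need not change: CMH has about 79% power at 173 per arm even with non-prognostic strata, essentially that of the χ² test on which the calculation rests.

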### Potential benefits and disadvantages of induction chemotherapy

Induction chemotherapy in addition to neoadjuvant chemo(re)irradiation has the potential to induce more local tumour downstaging than can be achieved with chemoradiotherapy alone owing to the supplementary effect of the induction chemotherapy, and possibly also the synergistic effect of induction chemotherapy and chemoradiotherapy^18^. Improved local downstaging may subsequently increase the R0 resection rate, which has been identified as the main prognostic factor for overall survival^6–8^. When local downstaging is excellent, a pathologic complete response (pCR) can be achieved, which is a predictive variable for survival in patients with LRRC^19^. With improved local downstaging, the proportion of patients with a pCR may also increase. Alongside the local effect, induction chemotherapy may also have the potential to eradicate micrometastases^20^.

The addition of induction chemotherapy also has potential drawbacks. First, induction chemotherapy is associated with toxicity^21^. Second, chemotherapy-induced morbidity could delay, reduce or prevent subsequent treatment with chemoradiotherapy and surgery. Third, when chemoradiotherapy is preceded by induction chemotherapy, the toxicity of chemoradiotherapy may be increased. Finally, the prolonged and intensified neoadjuvant course may influence the patient’s performance status and may have a negative effect on surgical morbidity and mortality rates. Furthermore, prolonged neoadjuvant treatment may increase the risk of disease progression and secondary unresectability.

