### Outcomes

The primary outcome of the study is the proportion of patients with a clear resection margin. A resection margin is considered clear (R0), if there are no tumour cells in any of the resection surfaces as determined by microscopy (resection margin more than 0 mm).

Secondary outcomes are:

3- and 5-year local re-recurrence-free survival, defined as the interval between surgery and local re-recurrence;3- and 5-year progression-free survival, defined as the interval between randomization and progression of local recurrence, local re-recurrence, distant metastases or death;3- and 5-year metastasis-free survival, defined as the interval between randomization and development of distant metastases;3- and 5-year disease-free survival, defined as the interval between surgery and local re-recurrence, distant metastases or death;3- and 5-year overall survival, defined as the interval between randomization and death;pathological response, graded according to the Mandard grading system^40^;radiological response, scored according to the magnetic resonance tumour regression grade (mrTRG);compliance rate with induction chemotherapy (i.e., the number of patients receiving CAPOX, FOLFOX or FOLFIRI as initial regimen will be tabulated, and dose modification and reason will be summarized for each regimen);toxicity of induction chemotherapy, scored from day 1 of the first cycle of induction chemotherapy until 1 month after the final administration, and graded according to the Common Terminology Criteria for Adverse Events (CTCAE) version 5.0;compliance rate with chemoradiotherapy, calculated as the total radiotherapy dose received divided by the total planned dose;toxicity of chemoradiotherapy, scored from start of radiotherapy until 3 months after the final dose of radiotherapy, and graded according to CTCAE version 5.0;number of patients undergoing surgery;surgical characteristics (e.g., type of resection, ostomy, use of intraoperative radiotherapy, blood loss, duration of operation, intraoperative complications);major surgical morbidity rate scored from the date of surgery to 3 months after surgery, and graded according to the Clavien–Dindo classification^41^;quality of life, assessed with EQ-5D-5L™, QLQ-C30 and QLQ-CR29 questionnaires at inclusion, and at 3 and 12 months after surgery; andcost-effectiveness and cost–utility, based on Dutch costing guidelines for healthcare, the case report forms, and the EQ-5D-5L™ questionnaire.

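### Local re-recurrence-free and disease-free survival are compared between arms only in operated patients and from surgery, so these two secondary comparisons are not randomized and can be biased in either direction

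*Protocol article*

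**What the plan says.** Under Outcomes, the protocol article lists "3- and 5-year local re-recurrence-free survival, defined as the interval between surgery and local re-recurrence" and "3- and 5-year disease-free survival, defined as the interval between surgery and local re-recurrence, distant metastases or death". Both clocks start at surgery, and the first definition does not name death as an event.

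Under Statistical methods, the population is fixed: "Local re-recurrence free survival and disease-free survival analyses will include only patients who underwent surgery". The same section covers all survival curves when it says that "the log rank test will be used to compare treatment arms, adjusting for stratification factors at randomisation" and that "hazard ratios will be calculated using a Cox proportional hazards regression model, adjusting for stratification factors". Those factors are previous radiotherapy, previous systemic therapy and expert centre. All tests are two-sided, with P below 0.05 called significant. The two operated-only endpoints are therefore set up as inferential comparisons between arms.

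Metastasis-free, progression-free and overall survival are timed from randomization and analysed by intention to treat. The number of patients operated on is a secondary outcome in its own right, compared by intention to treat with Fisher's exact test.

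**The concern.** Membership of the operated group is decided after randomization, by a process that the allocated treatment can change. The article gives reasons for a change in both directions:

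- **Fewer reach surgery after induction.** The section on potential benefits and disadvantages warns that "chemotherapy-induced morbidity could delay, reduce or prevent subsequent treatment with chemoradiotherapy and surgery" and that "prolonged neoadjuvant treatment may increase the risk of disease progression and secondary unresectability".
- **More reach surgery after induction.** The same section hopes for more local downstaging and eradication of micrometastases.
- **An extra exit.** Under Induction chemotherapy, restaging midway through induction can move a patient to palliative treatment. The control arm has no such step; the restaging after chemoradiotherapy is common to both arms.

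The loss is not random with respect to outcome. Sample size states that "25 per cent of patients who start neoadjuvant chemotherapy are not eligible for surgery owing to progressive disease". The two operated groups may thus differ in tumour behaviour that emerges after randomization, and adjusting for three baseline factors does not remove that difference. A clock starting at surgery also leaves out pre-operative failures and the unequal time taken to reach surgery.

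Most is at stake for local control. The Discussion expects a higher R0 rate to improve local re-recurrence-free and overall survival. Overall survival is compared in all randomized patients, but local re-recurrence-free survival is compared only in this selected group.

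**Working it through.** **1. The plan's own figures.** Sample size takes 75% reaching surgery and R0 in 60% of those: 0.75 × 0.60 = 0.45, the stated control rate. A recalculation for 45% versus 60% (two-sided 5%, 80% power) reproduces 173 per group, with power 80.05%. No event count or power is given for the two operated-only endpoints. At 25% loss, 0.25 × 364 = 91 patients fall outside these analyses and 273 remain, about 137 per arm.

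**2. Planned time to surgery.** Take 4 weeks to start (the upper limit), 5 weeks of radiotherapy, and mid-window values of 4 weeks from the last induction cycle to chemoradiotherapy and 12 weeks from chemoradiotherapy to surgery.
- Control: 4 + 5 + 12 = 21 weeks.
- CAPOX, four cycles: the last cycle starts 9 weeks in, so 4 + 9 + 4 + 5 + 12 = 34 weeks.
- FOLFOX or FOLFIRI, six cycles: 4 + 10 + 4 + 5 + 12 = 35 weeks.

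The start and radiotherapy terms cancel, leaving a difference of 13 to 14 weeks. This applies to patients with stable or responsive disease; those with local progression stop induction early, and their difference is shorter.

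**3. Selection effect from the article's figures.** The Introduction gives 5-year survival of 48–58% after R0 and 10–18% after R1/2. Overall survival stands in here for the two endpoints, whose rates are not given. Assume that the experimental arm loses x more patients, all of whom would have been R1/2, and gains no R0 resections.

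Survival among operated = [0.45 × S(R0) + (0.30 − x) × S(R1/2)] / (0.75 − x)

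| x | R0 among operated | Low figures (48%, 10%) | High figures (58%, 18%) | Approximate HR |
|---|---|---|---|---|
| 0 | 0.45/0.75 = 60% | 0.246/0.75 = 32.8% | 0.315/0.75 = 42.0% | 1 |
| 0.05 | 0.45/0.70 = 64.3% | 0.241/0.70 = 34.4% | 0.306/0.70 = 43.7% | 0.96, 0.95 |
| 0.10 | 0.45/0.65 = 69.2% | 0.236/0.65 = 36.3% | 0.297/0.65 = 45.7% | 0.91, 0.90 |

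HR is ln(S experimental)/ln(S control). No patient has benefited in any row.

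**4. Both directions, by simulation.** Assumptions not in the article: half the patients are poor-prognosis, 3-year disease-free survival is 20% (poor) or 60% (good), censoring is at 5 years, control loss is 25%, and treatment has no effect on any patient's post-operative hazard. There were 182 randomized per arm and 4,000 runs of an unstratified log-rank test in operated patients.

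If all losses are poor-prognosis, expected 3-year disease-free survival in operated controls is (0.50 × 0.60 + 0.25 × 0.20)/0.75 = 46.7%.

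| Experimental loss | Expected 3-year value, experimental | Simulated HR | Rejection at 5% | Of which favouring experimental |
|---|---|---|---|---|
| 15% | (0.30 + 0.35 × 0.20)/0.85 = 43.5% | 1.08 | 9.0% | 0.6% |
| 25% | 46.7% | 1.00 | 4.8% | 2.3% |
| 30% | (0.30 + 0.20 × 0.20)/0.70 = 48.6% | 0.95 | 6.4% | 5.4% |
| 35% | (0.30 + 0.15 × 0.20)/0.65 = 50.8% | 0.90 | 10.8% | 10.4% |

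If three quarters of losses are poor-prognosis, the HR is 1.04 at 15% loss and 0.95 at 35%. If loss is unrelated to prognosis, it is about 1.00 throughout.

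**The case against.** The case for leaving the plan alone has real weight. Local re-recurrence can occur only after resection, so the from-surgery definition has a clear clinical meaning. Both endpoints are secondary. Progression-free survival, from randomization and by intention to treat, already counts local progression, re-recurrence, metastasis and death, so it is close to a randomized version of disease-free survival. Unequal loss before surgery would show in the intention-to-treat comparison of the number operated on, and could also show in progression-free survival and the intention-to-treat R0 rate.

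All of this stands, and it limits the point. It does not remove it: P values remain prescribed for two selected comparisons, and the article states no all-randomized analysis of local control.

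A reader might go further and infer that the plan favours induction. The article does not support that. It gives reasons for more and for fewer patients reaching surgery, and if induction brings more poor-prognosis patients to surgery, the bias runs against it. A reader might also infer that the main oncological support for R0 is compromised. The article does not rank its long-term outcomes, and the Discussion names local re-recurrence-free and overall survival, not disease-free survival.

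**Conclusion.** The point holds at moderate severity. The planned comparisons of local re-recurrence-free and disease-free survival are conditional on a post-randomization outcome that treatment can change, and adjustment for stratification factors does not repair this. The direction depends on which arm loses more poor-prognosis patients. The bias disappears if loss is equal in amount and kind, or unrelated to prognosis.

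For a 10-point difference in loss, the apparent hazard ratio under no effect is about 0.90 or 1.08, with false-positive rates of 10.8% and 9.0%. For 5 points more loss in the experimental arm, it is about 0.95 with 6.4%. These sizes come from the extreme case in which every lost patient is poor-prognosis, and from assumed survival rates; they show the possible scale and predict nothing.

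The substantive gap is local control. The primary endpoint and progression-free, metastasis-free and overall survival are untouched, so this is not a fault that undermines the trial's main conclusions.

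**What to change.** 1. Report the operated-only, from-surgery curves for both endpoints by arm as descriptive, non-randomized summaries without P values. Base between-arm inference for disease-free survival on the existing intention-to-treat progression-free survival; a re-timed disease-free survival would largely duplicate it.

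2. Add a local-failure endpoint from randomization in all randomized patients. Count local progression to unresectability, no resection or R2 resection, and local re-recurrence as events. Treat death and distant metastases without local failure as competing events. A patient left unresected because of metastases meets both descriptions, so the text must say which takes precedence.

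3. Fix one event-dating rule for both arms that does not import the roughly 13-week difference in planned time to surgery. One option is a common landmark from randomization at which failure to achieve local clearance is dated. It should lie beyond the latest planned surgery in either arm: at the upper window limits, 4 + 10 + 5 + 5.6 + 14 = 38.6 weeks (28 fractions, assuming five a week and no delays).

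The cost is small. Progression, metastasis and death are already needed for progression-free survival, and resection status for the primary endpoint. There is a little more analysis work, and the new endpoint compares less directly with surgical series, which the descriptive curves still allow.
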